#### Weight

7. Body mass index (BMI) less than 30 Kg/m^2

#### Sex and Contraceptive/Barrier Requirements

8. Female participants with suspected or documented menopause
  - a. Peri- or post-menopausal, defined as having no menstrual periods for at least 12 months prior to study entry, or skipping at least one menstrual period in the 12 months prior to study entry. Peri- or post-menopausal status will be determined for candidates who have had the uterus removed by an assessment of blood follicle stimulating hormone (FSH). Women with an FSH level higher than 30 mIU/mL will be eligible for the study.

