| Study drug titration to twice a day                                                                                                                                                   |                                                 |                                          | X        |                        |           |           |           |           |            |            |                  |
| Contraceptive and Barrier Guidance                                                                                                                                                    | X                                               |                                          |          |                        |           |           |           |           |            |            |                  |
| Advice for healthy lifestyle and physical exercise                                                                                                                                    |                                                 | X                                        |          |                        |           | X         |           | X         |            |            |                  |
| Inform about reasons for temporary or definitive discontinuation of the study drug                                                                                                    |                                                 | X                                        |          |                        |           | X         |           | X         |            |            |                  |

| Procedure                                                                                                                                                                                                                             | Screening
(up to 30
days before
Day 0) | Intervention Period, Visit number [Week] |          |                        |           |           |           |           |            |            | E/D  |

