**Other Exclusions**

12. Pregnant or breastfeeding women, women wishing to conceive or unwilling to commit to contraceptive methods.
13. Any comorbidities or treatment with experimental drugs that according to the investigator could bias study results or entail additional risks for the participant.

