## **7. Discontinuation of Study Intervention and Participant Discontinuation/Withdrawal**

### **7.1. Discontinuation of Study Intervention**

In some instances, it may be necessary for a participant to permanently discontinue study intervention. If study intervention is permanently discontinued, every effort should be made to keep the participant in the study for safety follow-up. See the SoA for data to be collected at the time of discontinuation of study intervention and follow-up and for any further evaluations that need to be completed.

At the baseline visit, patients will be given a list of precautions and reasons for temporarily or permanently discontinuing study medication, as well as a form of contact with the investigator.

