#### **7.1.1. Permanent Discontinuation**

Study medication must be permanently discontinued in the following circumstances:

- Diabetes onset
- Hypersensitivity to the active substance or to any of the excipients.
- Unrecovered severe renal failure (eGFR <45 ml/min).
- Any acute metabolic acidosis event (such as lactic acidosis, diabetic ketoacidosis).
- Adverse events or intolerances related to the study medication, at the investigator's discretion.
- Diagnosis of B or C hepatitis infection or any other progressive liver disease.
- Diagnosis of chronic heart failure, or cancer.
- Alcohol abuse:
  - For men, heavy drinking is typically defined as consuming 15 drinks or more per week.
  - For women, heavy drinking is typically defined as consuming 8 drinks or more per week.
- Participants starting other maintenance medications that according to study drug label are contraindicated with metformin. (Appendix 7)
- Pregnancy.
- Any new events, comorbidities or medications that according to the investigator could entail additional risks for the participant.

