## **10.5. Appendix 5: Contraceptive and Barrier Guidance**

### **10.5.1. Definitions**

#### **Women of Childbearing Potential (WOCBP)**

A woman is considered fertile following menarche and until becoming postmenopausal unless permanently sterile (see below):

If fertility is unclear (eg, amenorrhea in adolescents or athletes) and a menstrual cycle cannot be confirmed before first dose of study intervention, additional evaluation should be considered.

Women in the following categories are not considered WOCBP:

- Premenarchal
- Premenopausal female with 1 of the following:
  - Documented hysterectomy
  - Documented bilateral salpingectomy
  - Documented bilateral oophorectomy

For individuals with permanent infertility due to an alternate medical cause other than the above (eg, Mullerian agenesis, androgen insensitivity), investigator discretion should be applied to determining study entry.

Note: Documentation can come from the site personnel's review of the participant's medical records, medical examination, or medical history interview.

- Postmenopausal female

A postmenopausal state is defined as no menses for 12 months without an alternative medical cause. Peri- or post-menopausal status will be determined for candidates who have had the uterus removed by an assessment of blood follicle stimulating hormone (FSH). Women with an FSH level higher than 30 mIU/mL will be eligible for the study. See participant libraries for common text to include here.

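### Criterion 8 admits perimenopausal women whom Appendix 5 still classes as of childbearing potential, and pregnancy is an exclusion, but no laboratory pregnancy test is scheduled before the first dose

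*Protocol*

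**What the plan says.** Criterion 8 in Protocol 5.1 has two routes to peri- or postmenopausal status: no periods for at least 12 months, "or skipping at least one menstrual period in the 12 months prior to study entry". It ties FSH measurement to candidates whose uterus has been removed.

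Appendix 5 defines childbearing potential: "A woman is considered fertile following menarche and until becoming postmenopausal unless permanently sterile (see below"). It then sets the boundary: "A postmenopausal state is defined as no menses for 12 months without an alternative medical cause".

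Criterion 12 in 5.2 excludes "Pregnant or breastfeeding women, women wishing to conceive or unwilling to commit to contraceptive methods". Section 7.1.1 opens its list with "Study medication must be permanently discontinued in the following circumstances", and pregnancy is on that list. It is also a withdrawal reason in 7.2.

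The Schedule of Activities (1.3) contains these related items:
- review of inclusion and exclusion criteria at screening and week 0;
- FSH and menopause history at screening, with a footnote limiting FSH to women who have had no period in the last year;
- "Contraceptive and Barrier Guidance" at screening;
- "Inform about reasons for temporary or definitive discontinuation of the study drug" at weeks 0, 48 and 96.

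Section 7.1 adds that at baseline "patients will be given a list of precautions and reasons for temporarily or permanently discontinuing study medication", with a means of contacting the investigator.

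Appendix 5 also asks sites to consider further evaluation before the first dose when fertility is unclear and a menstrual cycle cannot be confirmed. Appendix 2 allows extra tests at the investigator's discretion or where local rules require them. Section 8 allows unscheduled samples for safety.

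**The concern.** The protocol chooses to admit women whom its own appendix regards as fertile, and it treats pregnancy as serious enough to bar entry and to end treatment permanently. One would then expect an objective check before the first tablet. Section 5 forbids eligibility waivers, and section 8 requires that screening evaluations be completed and reviewed to confirm every eligibility criterion. For pregnancy, no laboratory evaluation is scheduled that could supply that confirmation. At a site that follows the schedule exactly, the answer comes from the participant's account, and a woman with irregular cycles may not recognise an early pregnancy. At stake is exposure to study drug in a participant whom the protocol meant to exclude.

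**Working it through.** The protocol states no figure on this point. The check sets the sections side by side and counts scheduled tests.

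1. **Who is eligible.** Take a woman aged 50 or over who still menstruates, has skipped one period in the past 12 months, has a uterus and has not been sterilised. She satisfies criterion 1 (age) and the second route of criterion 8.

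2. **How Appendix 5 classes her.** She has menstruated within 12 months, so she is not postmenopausal. None of the listed surgical exceptions applies. She is of childbearing potential.

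3. **Whether FSH settles her status.** It does not. Criterion 8 applies FSH to women without a uterus, and the Schedule footnote applies it to women with no period in the last year. She is in neither group.

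4. **Scheduled pregnancy tests.**
   - Schedule of Activities: 0
   - Visit lists in 8.1.1: 0
   - Table 2: 0 (the urinalysis row lists specific gravity, dipstick items and microscopy, without hCG)
   - Table 3: 0
   - Table 4: 0
   - Total: 0, including 0 at the two visits up to the first dose.

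5. **What checks the exclusion instead.** Eligibility is reviewed twice (screening and week 0), menopause history is taken once, contraceptive guidance is given once, a commitment to contraception is required, and Appendix 5 has its discretionary line. All of these work through history or judgement.

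6. **Whether a test needs a new specimen.** It does not. The full safety panel in the Schedule includes urine at screening and week 0, and the urinalysis row of Table 4 is marked at both: 2 of 2 columns up to the first dose.

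7. **Whether scheduled tests on treatment would add much.** From week 24 the visits are 48 − 24 = 72 − 48 = 96 − 72 = 24 weeks apart. With windows of ±7 days the gap can reach 24 weeks + 14 days = 26 weeks. A test tied to those visits could find a pregnancy that late. Testing when pregnancy is suspected is more useful, and section 8 and Appendix 2 already permit it.

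**The case against.** The strongest reply is that the pregnancy exclusion is already checked. Sites review the criteria at screening and again at week 0, take a menopause history, obtain a contraception commitment, and are told in Appendix 5 to consider further evaluation when fertility is unclear and a cycle cannot be confirmed. That stands against any claim that the exclusion goes unverified. It does not supply a laboratory result: the Appendix 5 line is discretionary, its examples are adolescents and athletes, and contraceptive advice cannot detect a pregnancy that already exists.

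A reader might also infer that the lack of scheduled tests on treatment is a defect. The documents do not support this. Unscheduled safety samples and additional tests are allowed at any time, participants are told the reasons for stopping, and visits 24 weeks apart are a poor vehicle for detection.

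A reader might take the unattached note 3 under Table 2, on urine versus serum testing, and the entry for hCG in the abbreviation list as proof that a test was planned and dropped. They may equally be template remnants. The note names no pregnancy test, and no table entry carries its marker. Nor is Table 2 exhaustive: FSH is scheduled but not listed there, so absence from Table 2 alone is weak evidence. The finding rests on absence from the Schedule, the visit lists and the tables together.

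Finally, admitting perimenopausal women under a contraception commitment does not contradict excluding pregnancy. This is an omitted safeguard, and no two statements in the protocol conflict. The small number of women likely to be concerned supports a low rating but does not remove the gap.

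**Conclusion.** The point holds as a minor, cheap safety improvement. Women whom the protocol classes as of childbearing potential can enter and receive the first dose with no scheduled laboratory pregnancy test (0 tests at 2 pre-dose visits). Their exclusion rests on history, eligibility review, a contraception commitment and a discretionary instruction.

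The size cannot be quantified. The protocol gives neither a sex distribution nor a pregnancy risk, and the number of women is assumed small because entry requires age 50 or over together with suspected or documented menopause. The consequence is limited to participant safety, and the primary analysis of epigenetic age acceleration is unaffected.

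The conclusion also assumes that Appendices 8 and 9, which by title cover lifestyle advice and reasons for stopping study drug and whose text could not be checked, contain no test schedule.

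**What to change.** Add one row to the Schedule of Activities and one entry to Table 2: a urine pregnancy test at baseline before the first dose, optionally also at screening, for women with less than 12 months of amenorrhoea and no permanent sterility. Run it on the urine already collected, and attach note 3 of Table 2 to the new entry so that the note has a referent.

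For the treatment period, at most a one-line reminder is needed that a test should be done when pregnancy is suspected, using the unscheduled sampling that section 8 and Appendix 2 already allow. Scheduled tests on treatment are not required.

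The cost is amendment wording plus one or two urine tests per woman concerned. No visit is added, and the pre-dose tests need no additional specimen.

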#### Informed Consent

9. Capable of giving signed informed consent as described in Appendix 1 which includes compliance with the requirements and restrictions listed in the informed consent form (ICF) and in this protocol.

### 5.2. Exclusion Criteria

Participants are excluded from the study if any of the following criteria apply:

**Medical Conditions**

1. Participants previously diagnosed with diabetes mellitus, prediabetes and body mass index > 30 kg/m^2.
2. Participants with chronic hepatitis B and/or active hepatitis C or concurrent active or progressive liver disease.
3. Participants with history of any of the following comorbidities: stroke, heart failure, dementia, myocardial infarction and cancer or history of lactic acidosis.
4. Participants with decreased tissue perfusion or hemodynamic instability due to infection or other causes
5. Participants with active alcohol abuse:
  - a. For men, heavy drinking is typically defined as consuming 15 drinks or more per week.
  - b. For women, heavy drinking is typically defined as consuming 8 drinks or more per week.
6. Participants unable to swallow study medication tablets during the treatment period.

**Prior/Concomitant Therapy**

7. Participants receiving other medications that according to study drug label are contraindicated with metformin.
8. Participants with hypersensitivity or intolerance to any of the components of the study interventions as determined by the investigator.

**Prior/Concurrent Clinical Study Experience**

9. Participants that are unwilling to abstain from participating in another interventional clinical trial during the study follow up.

**Diagnostic assessments**

10. Impaired renal function (estimated glomerular filtration rate <60 mL/min).
11. Liver laboratory abnormalities: alanine aminotransferase (ALT) over 5 times the upper limit of normal (ULN) or ALT over 3xULN and bilirubin over 1.5xULN or any verified Grade 4 laboratory abnormality that to the investigators criteria would affect the safety of the participant if included in the study.

**Other Exclusions**

12. Pregnant or breastfeeding women, women wishing to conceive or unwilling to commit to contraceptive methods.
13. Any comorbidities or treatment with experimental drugs that according to the investigator could bias study results or entail additional risks for the participant.

### **5.3. Lifestyle Considerations**

All participants will receive advice for healthy lifestyle and physical exercise. A specific lifestyle information sheet (see Appendix 7) will be dispensed at baseline visit, week 48 and week 96.

**5.3.1. Meals and Dietary Restrictions**

There are no meals and dietary restrictions.

In pharmacokinetics studies, food slightly reduces and delays metformin absorption, but its clinical relevance is unknown.

Taking metformin during or after meals improves tolerability and reduces gastrointestinal symptoms so it is strongly recommended.

Participant will receive dietary recommendations in lifestyle information sheet. (See Appendix 8)

**5.3.2. Caffeine, Alcohol, and Tobacco**

There are no caffeine, and tobacco restrictions. However, participants with alcohol abuse define in section 5.2 will be excluded. A specific lifestyle information sheet (see Appendix 8) will be dispensed at baseline, visit week 48 y week 96.

**5.3.3. Activity**

All participants will receive advice for healthy lifestyle and physical exercise. A specific lifestyle information sheet (see Appendix 8) will be dispensed at baseline, visit week 48 y week 96.

**5.4. Screen Failures**

Screen failures are defined as participants who consent to participate in the clinical study but are not subsequently randomly assigned to study intervention/entered in the study. A minimal set of screen failure information is required to ensure transparent reporting of screen failure participants to meet the Consolidated Standards of Reporting Trials (CONSORT) publishing requirements and to respond to queries from regulatory authorities. Minimal information includes demography, screen failure details, eligibility criteria, and any serious adverse event (SAE).

Individuals who do not meet the criteria for participation in this study (screen failure) may be rescreened. Rescreened participants should be assigned a new participant number for every screening/rescreening event.

**5.5. Participant Replacement Strategy**

Participants who withdraw from the study before receiving their first dose of study treatment or during the first 8 weeks of study medication due to AEs or intolerance to investigational product will be replaced, whereas participants who withdraw from the study after 8 weeks of the study medication will not be replaced.

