## 7.2. Participant Discontinuation/Withdrawal from the Study

- In accordance with the current revision of the Declaration of Helsinki (Fortaleza, Brazil October 2013) (World Medical Association. Declaration of Helsinki- Ethical principles for medical research involving human subjects. *World Med Assoc.* 2013) a participant may withdraw from the study at any time at his/her own request without prejudice to the medical care provided by his doctor or referral centre in the future; or may be withdrawn at any time at the discretion of the investigator for safety, behavioral, or compliance reasons. This is expected to be uncommon. Specific reasons for withdrawal:
  - Participant withdraws consent.

- The participant is not willing to comply with the procedures required in the protocol.
  - For safety reasons, especially the occurrence of an event that requires permanent discontinuation of the study medication (see above).
  - Intolerance to the study medication.
  - Pregnancy.
  - Subject is incorrectly included in the study based due to a screening failure.
  - At the discretion of the investigator for any other safety, behavioral, or compliance reasons based on good clinical practice guidelines and clinical judgment.
  - Lost to follow-up.
  - Transfer to another hospital does not necessarily imply withdrawal if the patient wishes to continue in the study and comply with the protocol.
  - A participant may be withdrawn from the study if any AE, SAE, or laboratory safety result occurs, regardless of its relationship to the study medication, that in the opinion of the investigator requires withdrawal because further treatment would jeopardize the safety of the participant.
- The reasons for participants not completing the study will be recorded in the case report form.
  - At the time of discontinuing from the study, if possible, an early discontinuation visit should be conducted, as shown in the SoA. See SoA for data to be collected at the time of study discontinuation and follow-up and for any further evaluations that need to be completed.
  - The participant will be permanently discontinued both from the study intervention and from the study at that time.
  - If the participant withdraws consent for disclosure of future information, the sponsor may retain and continue to use any data collected before such a withdrawal of consent.

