### 9.2. Sample Size Determination

Approximately 80 participants will be screened to achieve 30 randomly assigned to study intervention for an estimated total of 30 evaluable participants per intervention group.

A maximum of 40 participants will be randomly assigned to study intervention such that approximately 30 evaluable participants complete the study.

**Note:** “Enrolled” means a participant’s, or their legally acceptable representative’s, agreement to participate in a clinical study following completion of the informed consent process. Potential participants who are screened for the purpose of determining eligibility for the study, but do not participate in the study, are not considered enrolled, unless otherwise specified by the protocol.

We do not have prior information to estimate the sample size accurately. With 30 subjects per group, a confidence level of 95% we would be able to detect with a power of 80% an effect size greater than 0.8.

**Note:** “Enrolled” means a participant’s, or their legally acceptable representative’s, agreement to participate in a clinical study following completion of the informed consent process and screening. Potential participants who are screened for the purpose of determining eligibility for the study, but do not participate in the study, are not considered enrolled, unless otherwise specified by the protocol.

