### 9.3. Analysis Sets

For the purposes of analysis, the following analysis sets are defined:

| Participant Analysis Set | Description                                                                                                                                            |
|--------------------------|--------------------------------------------------------------------------------------------------------------------------------------------------------|
| Randomized               | Participants who were assigned to one group of study intervention                                                                                      |
| Evaluable                | Participants who received at least 1 dose of study intervention                                                                                        |
| Safety                   | All randomized participants who are exposed to study intervention. Participants will be analyzed according to the intervention they actually received. |

| Defined Analysis Data Sets                                    | Description                                                                                                                                  |
|---------------------------------------------------------------|----------------------------------------------------------------------------------------------------------------------------------------------|
| Analysis set for primary estimand: Intention-to-treat-exposed | All randomized participants who are exposed to study intervention. For participants who discontinue study intervention and/or receive rescue |

|              |                                                                                                                                                                                       |
|--------------|---------------------------------------------------------------------------------------------------------------------------------------------------------------------------------------|
|              | therapy, all post discontinuation or post rescue observations will be included in the analysis set.                                                                                   |
| Per protocol | All randomized participants. For participants who discontinue study intervention and/or receive rescue therapy, post discontinuation or post rescue observations will not be included |

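### Dosed participants who leave within 8 weeks for adverse events or intolerance are replaced, so a loss of primary outcomes that may differ between arms is masked by a full-looking sample

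*Protocol*

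**What the plan says.** Section 5.5 replaces anyone who withdraws before the first dose, and also those who withdraw "during the first 8 weeks of study medication due to AEs or intolerance to investigational product will be replaced". Beyond that window, "participants who withdraw from the study after 8 weeks of the study medication will not be replaced".

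Section 9.3 defines the analysis set for the primary estimand as "All randomized participants who are exposed to study intervention", and for those who stop drug or receive rescue "therapy, all post discontinuation or post rescue observations will be included in the analysis set". The evaluable set is "Participants who received at least 1 dose of study intervention". Section 9.2 counts its target of 30 per group in evaluable participants.

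Section 7.2 gives "Intolerance to the study medication" among the reasons for withdrawal from the study and states: "The participant will be permanently discontinued both from the study intervention and from the study at that time". Section 7.1, by contrast, asks that people who stop drug be kept in the study, though for safety follow-up. Section 7.1.3 continues scheduled visits after long interruptions.

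The Schedule of Activities (section 1.3) places epigenetic sampling at weeks 0, 48, 96 and 144 and leaves the early-discontinuation column empty. The research-laboratory row of Table 4 in Appendix 2 shows the same pattern.

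**The concern.** The trigger for replacement comes after randomisation and after exposure, and it depends on how the participant fared on treatment. The 8-week window includes the start of dosing and the week 4 titration step. Section 6.5 itself provides for gastrointestinal events after that step, so early loss that differs between arms is foreseeable.

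A primary set that promises observations after discontinuation will hold people for whom the schedule can yield none. If each is matched by a substitute who does supply data, the group size looks intact and a reader cannot see how many randomised, dosed people are missing from the week 96 comparison, or from which arm. At stake are the comparability of the arms and the visibility of the loss.

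**Working it through.** **1. The plan's own figure.** Section 9.2 claims 80% power for an effect size above 0.8 with 30 per group and 95% confidence. A two-sample t-test at two-sided 0.05 (sidedness is not stated) gives a detectable effect of 0.736 SD (0.723 by normal approximation). Power at 0.8 is 86.1% (87.3%). A detectable effect of 0.80 matches about 25 to 26 per group, for example 30 × (1 − 0.15) = 25.5. The stated figure is conservative, and this point does not depend on it.

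**2. Who supplies an outcome.** Take a participant dosed at week 0 who leaves the study at week 6 for intolerance.
- Section 9.3: in the primary set, and evaluable.
- Section 7.2: off drug and out of the study.
- Section 1.3: baseline epigenetic sample only.
- Section 9.4.2: the response is change in epigenetic age acceleration, so with no post-baseline value the participant adds nothing to the model.
- Section 5.5: replaced, and the substitute can be sampled at weeks 48, 96 and 144.

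**3. Does replacement cause the distortion?** Assume that 4 of 30 on metformin and 1 of 30 on placebo leave early. After one-for-one replacement, the share of exposed participants without an outcome is 4/34 = 11.8% against 1/31 = 3.2%. If metformin leavers would have had no benefit, the effect seen in those with data overstates the effect in all exposed metformin participants by these factors:
- with replacement: 1/(1 − 4/34) = 1.13
- without replacement: 1/(1 − 4/30) = 1.15

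The factor is no smaller without replacement. The 4/34 also assumes that every substitute tolerates the drug. If substitutes are lost at the same rate, the missing share is 4/30 = 13.3% either way. The distortion comes from the missing outcomes.

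**4. Size of the selection effect.** Let pM and pP be the early-loss proportions on metformin and placebo, and D the difference in outcome, in SD, between those who stay and those who leave, taken as equal in both arms. With no drug effect, the mean among stayers is shifted by p × D, so the contrast is biased by (pM − pP) × D. The false-positive rate is from the noncentral t with 30 per arm contributing data, at two-sided 0.05. All rates and all values of D are assumptions.

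| pM / pP | D = 0.25 | D = 0.5 | D = 1 |
|---|---|---|---|
| 5% / 0% | 0.013 SD (5.0%) | 0.025 SD (5.1%) | 0.05 SD (5.4%) |
| 10% / 3% | 0.018 SD (5.1%) | 0.035 SD (5.2%) | 0.07 SD (5.8%) |
| 20% / 3% | 0.043 SD (5.3%) | 0.085 SD (6.2%) | 0.17 SD (9.9%) |
| 30% / 5% | 0.063 SD (5.7%) | 0.125 SD (7.6%) | 0.25 SD (15.9%) |

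**5. What replacement buys.** Power at 0.8 SD with 30 randomised per arm, no top-up and leavers' outcomes lost:

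| With data (metformin / placebo) | Power |
|---|---|
| 28 / 30 | 84.9% |
| 27 / 29 | 83.6% |
| 26 / 29 | 82.8% |
| 24 / 29 | 81.2% |
| 21 / 28 | 77.5% |

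For 26 and 29, the equivalent equal group size is 2 × 26 × 29/55 = 27.4. The detectable effect is 0.777 at 27 per arm and 0.762 at 28, so about 0.77.

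These figures take 30 per group from section 9.2. The same section says "A maximum of 40 participants will be randomly assigned to study intervention", which does not fit 30 in each of two groups. That is a separate inconsistency, relevant here only because a cap limits the room for replacements.

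**The case against.** The strongest reply is that section 5.5 is an ordinary recruitment rule and that the rest of the protocol limits the damage. Section 5.5 applies only to people who leave the study, not to those who stop or reduce drug and stay. Section 6.5 offers a dose reduction for some gastrointestinal events, section 7.1 asks for retention, and section 7.1.3 keeps visits going. Most of this stands, and it means that not every early intolerance becomes a lost outcome. It does not close the gap, because section 7.2 lists intolerance, and events that require permanent discontinuation of drug, as reasons to leave the study, and the retention in section 7.1 is for safety.

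A reader might also infer four stronger things that the protocol does not support:
- *That replacement undoes the exposed intention-to-treat set.* Section 5.5 removes nobody from it.
- *That only drug-caused withdrawals are replaced.* The rule covers both arms, the definition of an adverse event in section 10.4.1 does not depend on relatedness, and withdrawals before dosing are replaced too.
- *That substitutes go to the vacated arm and so require unblinding.* The protocol does not say how a substitute is allocated. Section 6.3 describes central, concealed allocation and dispensing by an uninvolved third party.
- *That replacement inflates the effect by about 13%.* Step 3 shows that the missing outcomes do so, and only if there is a true effect that leavers would not share.

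**Conclusion.** The point holds in a limited form. People who have been dosed and leave within 8 weeks for adverse events or intolerance are in the primary set and already evaluable, yet the schedule gives them no PhenoAge outcome. Their substitutes do supply one, and how a substitute is allocated is not stated. The harm comes from the lost outcomes. Replacement conceals a loss that may be unequal.

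On assumed rates the bias is about 0.01 to 0.09 SD for metformin loss up to 20% and D up to 0.5 SD, with a false-positive rate of at most 6.2%. It reaches 0.17 to 0.25 SD, with rates of 9.9% to 15.9%, only when metformin loss is 20% to 30% and D is a full SD. The protocol gives neither loss rates nor any link between intolerance and epigenetic age change, so these figures show a range and predict nothing. Restricting replacement alone would remove none of this bias. Collecting the outcomes would.

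**What to change.** - **Section 5.5:** limit replacement to withdrawals before the first dose, who are outside the exposed set anyway. Alternatively, state that any added participant is newly randomised to the next concealed allocation and substitutes for nobody.
- **Section 9.3:** state that every dosed participant stays in the exposed intention-to-treat set, whether or not another participant is added.
- **Outcome collection:** state that, subject to consent, dosed participants are asked for the scheduled week 48, 96 and 144 samples after stopping study drug or leaving for intolerance.
- **Consistency:** reconcile sections 5.5, 7.1, 7.1.3, 7.2 and 9.3 on who remains in follow-up and who counts as evaluable.
- **Reporting:** give early leavers by arm, with reasons.

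The cost is a few sentences in several sections (a change to 5.5 alone would not obtain the samples) and some follow-up effort. If early leavers are neither topped up nor retained, a few outcomes are lost. With 5 lost of 60, power at 0.8 SD is still about 83% and the detectable effect moves from about 0.74 to about 0.77 SD. Power falls below 80% only with heavier loss, such as 21 and 28 with data.
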